### Comparison to Prior Work

Previous telementoring studies have primarily focused on demonstrating technical feasibility and safety rather than educational outcomes [13,14]. The SURGTEACH (Surgical Telementoring in Acquisition of Surgical Skills of Laparoscopic Cholecystectomy) trial extends this work using validated educational assessment tools (GOALS and NOTSS) and a randomized design. The author group of this pilot RCT has previously published a prospective clinical trial evaluating the educational role of ST in minimally invasive surgery [34]. Unlike observational studies that compare outcomes before and after telementoring implementation, this parallel-group design with a concurrent control arm will provide more rigorous evidence of any educational benefit.

The integration of the LapCo TT framework distinguishes this study from prior telementoring research, which often lacked standardized communication protocols. By training all mentors—both telementors and on-site mentors—in identical communication principles, we minimize the confounding effects of differing teaching styles and isolate the effects of the mentoring modality itself.

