### Technical Setup of the Telementoring System

Both hospitals, including patients in the study, have implemented ST systems in the ORs. The Olympus telecollaboration platform, MedPresence, provides a telementoring system that uses voice instructions delivered via headphones to assist the mentee throughout laparoscopic surgery. Simultaneously, the telementor observes the procedure in real time via a live stream from the laparoscopic camera. Telestration may be used, at the request of the telementor or the telementee, to provide annotations on a static picture of the ongoing surgical procedure. The telestration session begins when the telementor instructs the mentee to cease surgery and directs their attention to the visual aspect. Telementors may demonstrate surgical planes and strategize dissection.

The telementor may alternate between the external camera, which provides an overview of the laparoscopic trocars and the spatial positions of the OR and anesthesia nurse, and the laparoscopic camera. The system captures audio from the mentor-mentee dialog and footage from the laparoscopic surgery and the external camera. The external camera and its audio recording provide a foundation for assessing interactions between the telementee and OR staff, enabling the evaluation of the telementee’s nontechnical skills.

In both study arms, the standard operative team includes the operating resident, a camera-holding assistant (assisting surgeon), a scrub nurse, and a circulating nurse.

In the intervention group, the local assisting surgeon, an experienced laparoscopic surgeon, holds the laparoscopic camera and assists the operating resident solely by moving the camera to meet the resident’s demands, providing instructional guidance only when patient safety requires it. The camera-holding surgeon’s role is limited to emergency assistance. In the control arm, the on-site mentor, an experienced laparoscopic surgeon, is scrubbed and provides active instruction throughout the procedure, while the same support personnel configuration is maintained in the OR. Figure 3 shows the intraoperative setup during a telementored procedure in the intervention arm.

In the control arm, the Lapco principles of intraoperative communication and the GROW model are not applied during the mentor’s preoperative, intraoperative, and postoperative guidance of the mentee.

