#### Mentors

The eligibility criteria for the mentors are as follows:

Consultant surgeon with more than 5 years of experience performing LCs independentlyAcquainted with the assessment of videos for the GOALS score [27]Both telementors and on-site mentors had to attend the national LapcoNor TT course and follow standardized communication norms with the mentee during surgical mentoring, thus diminishing the bias of communicative difference.

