### Interventions

A skilled surgeon will serve as the camera-holding assistant for all procedures in the intervention group. They will intervene only at the time of unexpected events during surgery requiring emergency on-site assistance. Second, residents in the intervention group will receive postoperative coaching grounded in Lapco TT principles and the GROW model. In contrast, the control group will follow standard, unstructured guidance during the procedure. The mentors and mentees will sign a contract accepting the educational setting and the prerequisites before participating in the trial. Table 2 summarizes the intervention and control conditions.

**Table 2. T2:** Comparison of intervention and control groups.

Component	Telementoring group (intervention)	Traditional training group (control)
Mentor location	Remote via secure video link. May use a laptop or other mobile devices	Physically present in operating room
Verbal communication mode	Headphones with a mic during surgery for real-time mentor-mentee communication	Direct verbal communication; physical gestures
Visual guidance	Live stream of procedure. Possibility for static image annotation (telestration); verbal description of dissection planes	Direct pointing; hands-on demonstration capability
Mentor’s view	Laparoscopic camera feed + external OR^a^ camera.	Direct laparoscopic monitor view + peripheral vision of OR
Physical intervention	Not possible (local consultant available for emergencies)	Can take instruments to demonstrate; tactile guidance
Postoperative coaching	Mandatory structured GROW^b^ model session (15‐20 min)	Standard informal feedback (unstructured, variable).
Documentation	All sessions recorded; coaching documented	Standard operative notes only.

a OR: operating room.

b GROW: goals, reality, options, wrap-up.

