#### Intraoperative Mentoring

During the surgical procedure, an experienced consultant surgeon is physically scrubbed in alongside the resident. The primary mode of instruction is direct verbal guidance throughout the operation. Mentors retain discretion to physically interact during the case. They may guide the resident’s hands, indicate anatomical structures on the surgical screen, or temporarily assume control of instruments to demonstrate a specific technique. While the same standardized procedural steps are typically followed, the mentor provides teaching and feedback at their discretion, in the absence of a formalized, structured teaching framework.

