### The Surgical Procedure

The LC procedure was standardized using a stepwise approach, incorporating the principles of creating the critical view of safety before transecting any structure in Calot triangle [28,29]. All included residents were instructed in intraoperative communication in accordance with Lapco and GROW principles. A step-by-step procedure was provided for both mentees and mentors, and adherence was required. A detailed description of the step-by-step surgical procedure is provided in Multimedia Appendix 3.

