### Outcomes

#### Primary Outcomes

The primary outcomes are the GOALS and NOTSS scores (Figures 1 and 2). The GOALS score is the only global rating scale developed and validated for assessing laparoscopic surgery. Five subscales are assessed: depth perception, bimanual dexterity, efficiency, tissue handling, and autonomy. Each subscale is scored from 1 to 5, yielding a maximum score of 25 when assessing the resident’s laparoscopic technical skills. The NOTSS score assesses the operating surgeon’s nontechnical surgical skills by evaluating defined parameters [30].

The NOTSS score will be derived from video recordings of interactions between the operating telementee and the rest of the OR team. A 3-member evaluation group of specialized OR nurses will be established to assess the NOTSS score for each procedure by reviewing video footage from the room camera.

The GOALS score will be assessed by video recording the laparoscopic camera footage of each procedure performed by the included registrars. A 3-member evaluation group of expert laparoscopic surgeons will be established to assess the GOALS score for each procedure by reviewing the laparoscopic video footage, including the verbal communication between the mentee and the mentor.

Both evaluation groups will be presented with video footage of each included mentee in a random order to obtain blinded evaluations of the GOALS and NOTSS scores.

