### Strengths and Limitations

#### Strengths

This study represents the first randomized comparison of telementoring versus traditional training with a primary focus on educational outcomes. It employs validated, objective assessment tools, including GOALS and NOTSS, to ensure robust measurement of both technical and nontechnical skills. Outcome assessment is blinded through standardized video review, reducing the risk of assessor bias. Both study arms use a standardized communication framework, which minimizes variability in mentor–trainee interaction. In addition, postoperative coaching is delivered in a structured manner using the evidence-based GROW model. Randomization is stratified by trainee experience level, further strengthening internal validity and group comparability.

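### The article both requires and withholds Lapco communication in the control arm, and on either version the design does not isolate the mentoring modality

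*Protocol article*

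**What the plan says.** Several sections put the standardized communication framework in both arms:

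- Mentors (eligibility): "on-site mentors had to attend the national LapcoNor TT course and follow standardized communication norms with the mentee during surgical mentoring". The stated purpose is to reduce bias from differences in communication.
- Residents (eligibility): a resident must agree with the mentor on a communication model derived from LapcoNor. The criterion is not limited to one arm.
- The Surgical Procedure: "All included residents were instructed in intraoperative communication in accordance with Lapco and GROW principles".
- Strengths: "Both study arms use a standardized communication framework".

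Others keep it out of control:

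- Introduction: Lapco communication and GROW coaching are assigned to the intervention arm.
- Technical Setup of the Telementoring System: "In the control arm, the Lapco principles of intraoperative communication and the GROW model are not applied", whether before, during or after the operation.
- Interventions: control guidance during the procedure is described as unstructured.
- Control Group, Intraoperative Mentoring: the mentor teaches at discretion, "in the absence of a formalized, structured teaching framework".

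Postoperative coaching is not in dispute. Table 2 and the Postoperative Coaching section make a structured GROW session mandatory in the intervention arm. Table 2 and the Postoperative Feedback section give control an informal debrief at the mentor's discretion.

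Comparison to Prior Work then claims that, because telementors and on-site mentors had identical communication training, "we minimize the confounding effects of differing teaching styles and isolate the effects of the mentoring modality itself".

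**The concern.** The control condition is half of what the trial compares. If one section tells on-site mentors to use Lapco norms and another says those norms are not applied, the content of the comparison is unsettled in one important respect: whether structured intraoperative dialogue is common to both arms or belongs to the intervention.

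Two things are at stake. The first is attribution. A reader who accepts the isolation sentence would credit any GOALS difference to remote mentoring as such, when structured dialogue, GROW coaching or both could have produced it. The second is what passes to the definitive trial. The pilot's aims include a preliminary effect size for the next sample size calculation, and Statistical Analysis computes Cohen's d for that purpose. That figure can be used only if the later trial's control condition is known to match this one. Recruitment Status also shows inclusion still open, so sites reading different sections could teach the remaining control residents differently.

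**Working it through.** No figure in the article bears on this point, so the check is a comparison of its sections.

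**Step 1. Can the sections be reconciled?** The most favourable reading is that control mentors were trained in Lapco but did not apply it.

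- It fits Technical Setup, Interventions and Intraoperative Mentoring.
- It fits Limitations, which calls control standard care that may vary between mentors despite their training.
- It can be stretched to fit The Surgical Procedure (residents were instructed) and the first half of the Comparison to Prior Work sentence (mentors were trained), since instruction and training are not use.
- It does not fit Mentors, which requires on-site mentors to follow the norms while mentoring, or Strengths, which says both arms use a framework.
- It sits badly with Residents, which makes agreement on a LapcoNor-derived model a condition of entry in either arm.

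The direct conflict is therefore Mentors and Strengths, supported by Residents, against Introduction, Technical Setup, Interventions and Intraoperative Mentoring.

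**Step 2. Is modality isolated under either version?** Take modality to mean a remote mentor who cannot handle the instruments versus a mentor at the table who can.

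- *Version A, Lapco used in both arms.* Modality differs. Intraoperative communication framework is the same. Postoperative coaching differs: mandatory structured GROW versus a discretionary debrief. One component besides modality differs.
- *Version B, Lapco withheld from control.* Modality differs, communication framework differs, and postoperative coaching differs. Two components besides modality differ.

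Neither version leaves modality as the only difference. The isolation sentence fails under A because of GROW coaching, and under B because of GROW coaching and the communication framework.

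**Step 3. Does the claim agree with the article's own rationale?** The Abstract's Objective and the end of the Introduction define the intervention as telementoring together with structured coaching. Principal Findings and Interpretation rests the superiority hypothesis partly on more explicit structured dialogue and partly on GROW coaching, which it says traditional training does not usually provide. The article thus counts on these components to produce the effect, which is incompatible with saying that the comparison isolates modality. Limitations mentions variation between control mentors but not this bundling.

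**Step 4. How far has the trial gone?** Recruitment Status gives 5 residents on the first platform and 3 on the second by December 2025: 5 + 3 = 8 of the 10 planned. Whatever control teaching those residents received has already happened, so the corrected text must describe it.

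**The case against.** The strongest reply is that the trial's contrast is already clear. The Objective, the end of the Introduction, Study Design and Setting and Anticipated Outcomes all set telementoring plus postoperative coaching against traditional on-site mentoring. On that view the isolation claim is one loose Discussion sentence in a pilot whose Limitations section disclaims firm conclusions on effectiveness. Much of this stands. A reader might infer that the contrast as a whole cannot be identified, but the article does not support that. The package is stated repeatedly, and comparing a package is legitimate. What is unsettled is whether control includes Lapco dialogue, and what is wrong is the attribution in one sentence. Pilot status does not excuse either, because both are statements of fact about the design.

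A reader might also infer from Table 2's Documentation row, which gives control "Standard operative notes only" while intervention sessions are recorded, that control procedures are not filmed and cannot be scored. The article does not support this. Primary Outcomes says GOALS is "assessed by video recording the laparoscopic camera footage of each procedure performed by the included registrars", and that both evaluation groups receive footage of each included mentee. The row can be read as describing documentation of teaching, which matches the absence of formal documentation under Postoperative Feedback. The word *telementee* in the NOTSS description looks like loose usage. These are minor points to clarify.

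Finally, one might argue that Lapco use in control shrinks the 3- to 5-point GOALS difference and leaves the planned 12 per group too few. The article gives nothing from which to estimate such dilution, and under the Technical Setup version there is none. No power or sample size consequence is claimed.

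**Conclusion.** The point holds. The current text both requires and withholds Lapco communication in control, and the claim to isolate the mentoring modality is wrong on either version. Its size is qualitative: one component besides modality differs between arms if Lapco is shared, and two if it is not.

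The conclusion rests on reading Mentors and Strengths as they are written. If those two are drafting slips and control was unstructured throughout, the contradiction is settled but the isolation claim is further from true. If control mentors did use Lapco, the isolation claim still fails on coaching alone.

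The randomized comparison of the package with on-site mentoring and the feasibility aims are not undermined. What must change is the description of control and the causal statement made about the comparison.

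**What to change.** - State one definition of control-arm communication, matching what was delivered to residents already included. Align Introduction, Technical Setup, Residents, Mentors, Interventions with Table 2, Control Group, The Surgical Procedure and Strengths to it. If delivery varied between residents, say so.
- In Comparison to Prior Work, replace the isolation claim with the effect of the combined package (telementoring, structured dialogue and GROW coaching) versus on-site mentoring as delivered. If Lapco was in fact used in both arms, say that structured dialogue is common to them. Either wording can agree with the Objective.
- If control teaching was unstructured, delete the shared-framework strength.
- As a minor clarification, reword Table 2's Documentation row to report what was actually recorded in each arm, and replace *telementee* in the NOTSS description with a term covering residents in both arms, so that both agree with the rest of Primary Outcomes.
- Optionally, describe how far Lapco steps were used in each arm. GOALS scoring already calls for footage that includes the dialogue between mentor and mentee, so no new data collection is needed, only rater time.

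The required changes are wording. The price is a narrower causal claim: the trial speaks to the package, and separating modality from coaching or dialogue would need a different design.

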### Strengths and Limitations

#### Strengths

This study represents the first randomized comparison of telementoring versus traditional training with a primary focus on educational outcomes. It employs validated, objective assessment tools, including GOALS and NOTSS, to ensure robust measurement of both technical and nontechnical skills. Outcome assessment is blinded through standardized video review, reducing the risk of assessor bias. Both study arms use a standardized communication framework, which minimizes variability in mentor–trainee interaction. In addition, postoperative coaching is delivered in a structured manner using the evidence-based GROW model. Randomization is stratified by trainee experience level, further strengthening internal validity and group comparability.

#### Limitations

As a pilot study, the relatively small sample size limits statistical power and precludes definitive conclusions regarding effectiveness. Blinding of participants is not feasible given the nature of the intervention, which introduces a potential risk of performance bias. The single-country setting may restrict the generalizability of the findings to other health care systems and training environments. The superiority hypothesis is based on an assumed benefit of structured telementoring that may not be fully realized in the final outcome assessment. Furthermore, a change in the technological platform during recruitment, from MedPresence to Proximie, may introduce heterogeneity in the intervention. The control group receives standard care, which may vary between mentors despite Lapco TT training, potentially increasing intermentor variability. Finally, assessing short-term outcomes limited to the first 5 procedures may not adequately capture long-term skill acquisition or retention.

### Future Directions

The results of this pilot study will directly inform the design of a definitive multicenter RCT. Specific aspects that may require modification include recruitment strategies, randomization procedures, outcome timing, and telementoring protocols. If substantial technical or logistical barriers are identified, alternative technological solutions will be explored before the definitive trial.

Beyond the immediate next steps, successful demonstration of telementoring efficacy could enable expansion to other laparoscopic procedures, support the development of national telementoring networks for rural surgical training, and inform educational policy for surgical residency programs in geographically challenging regions.

### Conclusion

The SURGTEACH trial is the first known randomized pilot trial to evaluate ST as an educational method. Globally and domestically, there are constraints on the number of surgeons available and strain on the surgical education system. The Norwegian health care system requires support to train sufficient surgeons, primarily due to geographical constraints and limitations in the education system. Therefore, there is a need for a fundamental change in surgical education, and ST has the potential to overcome these obstacles. This study has the potential to provide substantial evidence to enhance surgical education, particularly in rural health care facilities.
